### Recruitment rates and milestones

#### Original recruitment rates

Figure 2 shows the original projected recruitment of centres and participants, and projected number of women to be approached. Three centres will be established relatively early in the project followed by roll out to the others over the subsequent months.

**Fig. 2 Fig2:**
[figure not shown]
Original recruitment projection

The participant recruitment graph in Fig. 2 has been modelled to take into account: the phased rollout to the centres over the first 18 months; that there will be lags between the approach to women when they are in hospital for preassessment and their admission for operation; and that there are likely to be fewer operations around August and over Christmas (due to holidays).

### Revised recruitment rates with extension

Due to the slower than anticipated recruitment in the Uterine Trial a 15-month extension has been approved by the TSC and DMC oversight groups and funder (February 2015). The Uterine Trial is currently averaging 15 randomised participants per month. The Vault Trial will continue to recruit (beyond the original target) during this extension. A revised recruitment graph detailing changes to both the Vault and Uterine Trials is shown in Fig. 3.

**Fig. 3 Fig3:**
[figure not shown]
Revised recruitment projection

In summary, we aim to recruit 910 women to the randomised trials (630 to the Uterine Trial and 280 to the Vault Trial).

### Organisation

It is anticipated that there will be 3-monthly project management meetings, five meetings of the Steering Committee and four of the DMC. Two meetings are planned for collaborators (including gynaecologists, local research nurses, consumer participants and members of BSUG), the first is timed to occur when all the sites have been identified and the second when the results are available.

These time-related milestones will be used to enable close monitoring of progress.

### Local organisation in centres

Lead gynaecologist (local PI)Each collaborating centre will identify a lead gynaecologist who will be the point of contact for that centre. The responsibilities of this person will be to:establish the study locally (e.g. by obtaining agreement from clinical colleagues; facilitate local regulatory approvals; identify, appoint and train a local research nurse; and inform all relevant local staff about the study (e.g. other consultant gynaecologists, junior medical staff, secretaries, ward staff))take responsibility for clinical aspects of the study locally (e.g. if any particular concerns occur)identify which RCT the woman is eligible to participate in (vault or uterine), explain the different surgery options to them, and ensure that study documentation has been provided and that informed consent has been obtainednotify the Study Office of any unexpected clinical events which might be related to study participationprovide support, training and supervision for the local research nurse(s)represent the centre at the collaborators’ meetingsLocal research nurseEach collaborating centre will appoint a local research nurse to organise the day-to-day recruitment of women to the study. The responsibilities of this person will be to:keep regular contact with the local lead gynaecologist, with notification of any problem or unexpected developmentmaintain regular contact with the VUE Study Officekeep local staff informed of progress in the studycontact potential participants by: providing the Patient Information Sheet to women being admitted electively for prolapse surgery; identifying any eligible women at preassessment clinics or on the ward while they are in hospital for their prolapse surgery; explain the study and the potential for participation in a trial if they are eligible; explaining what is intended by research access to their NHS data; and describing the possibility of long-term follow-up and participation in other researchobtain the woman’s written consentkeep a log of whether eligible women are recruited or not (with reasons for nonparticipation)collect baseline data describing the women, log this information in the web-based VUE database and send paper copies to the Study Office along with the original signed Consent Formsuse this information to randomise the women using the web-based VUE databaseensure operative and postoperative data are collected and recorded in the web-based VUE database, and send paper copies to the Study Officefile relevant study documentation (e.g. Consent Forms, POP-Q results) in the woman’s medical recordsorganise and supervise alternative recruiters in case of holiday or absencerepresent the centre at the collaborators’ meetings

### Study coordination

#### The Study Office team

The Study Office is in CHaRT, Health Services Research Unit in Aberdeen and provides day-to-day support for the clinical centres. It is responsible for all data collection (such as mailing questionnaires), follow-up, data processing and analysis. It is also responsible for providing and maintaining the randomisation service, and communicating with the sites about VUE-specific issues. We will produce a yearly VUE newsletter for participants and collaborators to inform everyone of progress and maintain enthusiasm.

The VUE Study Office Team (Aberdeen-based grant holders and Study Office members) will meet formally at least monthly during the course of the study to ensure smooth running and trouble-shooting.

### The Project Management Group (PMG)

The study is supervised by its PMG. This consists of the grant holders and representatives from the Study Office. Observers may be invited to attend at the discretion of the PMG. We plan to meet or hold a teleconference every 3 months on average.

### The Trial Steering Committee (TSC)

The study is overseen by an independent Trial Steering Committee (TSC). The membership comprises the four independent members (including the chair), the chief investigator (CI) and grant holders. Observers or members of the sponsors (University of Aberdeen and NHS Grampian) and the funders (the HTA) may also attend, as may other members of the VUE Study Office or members of other professional bodies at the invitation of the chair. It is anticipated that the TSC will meet on five occasions.

### Research governance

The trial will be run under the auspices of CHaRT based at the Health Services Research Unit, University of Aberdeen. This will ensure compliance with research governance, and provide centralised trial administration, database support and economic and statistical analyses. CHaRT is a registered Clinical Trials Unit with particular expertise in running multicentre RCTs of complex and surgical interventions.

The CI will ensure, through the TSC, that adequate systems are in place for monitoring the quality of the study (compliance with Good Clinical Practice (GCP)) and appropriate expedited and routine reports of adverse effects, to a level appropriate to the risk assessment of the study.

### Data protection

The trial will comply with the Data Protection Act 1998 and regular checks and monitoring are in place to ensure compliance. Data are stored securely in accordance with the Act and archived to a secure data storage facility. The Consent Form will state that other researchers may wish to access (anonymised) data in the future. The senior IT manager (in collaboration with the trial statistician) will manage access rights to the data set. Prospective new users must demonstrate compliance with legal, data protection and ethical guidelines before any data are released. We anticipate that anonymised trial data will be shared with other researchers to enable international, prospective meta-analyses.

### Sponsorship

The study is cosponsored by the University of Aberdeen and NHS Grampian.

### Retention of data

It is intended to follow up the whole cohort of women for at least 10 years, and data will be retained as long as necessary for this purpose. Permissions will be sought from the relevant research governance bodies and the Ethics Committee. Attention has recently been drawn to the importance of long-term follow-up, especially in the study of pelvic floor dysfunction [15].

### Data and safety monitoring

#### Data Monitoring Committee

A separate and independent Data Monitoring Committee (DMC) will be convened. It is anticipated the members will meet once to agree terms of reference and on at least three further occasions to monitor accumulating data and oversee safety issues. This committee will be independent of the study organisers and the TSC. During the period of recruitment to the study, interim analyses will be supplied, in strict confidence, to the DMC, together with any other analyses that the committee may request. This may include analyses of data from other comparable trials. In the light of these interim analyses, the DMC will advise the Steering Committee if, in its view:One of the methods of prolapse surgery has been proved, beyond reasonable doubt, to be different from the control (standard management) for all or some types of women (in respect of either effectiveness or unacceptable safety concerns)The evidence on the economic outcomes is sufficient to guide a decision from health care providers regarding recommendation of which operation to choose

The TSC can then decide whether or not to modify intake to the trial. Unless this happens, however, the TSC, PMG, clinical collaborators and Study Office staff (except those who supply the confidential analyses) will remain ignorant of the interim results.

The frequency of interim analyses will depend on the judgement of the chair of the DMC. However, we anticipate that there might be two interim analyses and one final analysis.

The chair and the other independent members are to be appointed after confirmation by the HTA.

### Safety concerns

The VUE trial involves surgical operations for prolapse which are well-established in clinical practice. Adverse effects may occur after any type of prolapse surgery. The relevant guidelines for reporting SAEs will be followed.

Collaborators and participants may contact the chair of the TSC through the Study Office about any concerns they may have about the study. If concerns arise about procedures, participants or clinical or research staff (including risks to staff) these will be relayed to the chair of the DMC.

### Safety - definitions

An adverse event (AE) is defined as any untoward medical occurrence in a participant, not necessarily having a causal relationship.

All related SAEs and AEs will be recorded. Unrelated SAEs or AEs will not be recorded.

Within VUE, an SAE or AE is defined as ‘related’ if it occurs as a result of a procedure required by the protocol (i.e. prolapse surgery), whether or not this procedure is the specific intervention under investigation and whether or not it would have been administered outside the study as normal care.

Adverse events are not signs or symptoms of the disease being studied (in this case uterine or vault prolapse).

An AE is defined as ‘serious’ (SAE) if it:results in deathis life-threateningprolongs inpatient hospitalisation*requires hospitalisation*results in persistent/significant disability/incapacity, oris otherwise considered medically significant by the investigator

*Hospitalisation is defined as any overnight hospital admission or day-case admission.

Adverse events which are expected after prolapse surgery are listed below. Any AEs which are deemed to be related and serious but unexpected (i.e. not on the list below) will require expedited onward reporting to the sponsor.

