## Abstract

**Background:**

One in three women who have a prolapse operation will go on to have another operation, though not necessarily in the same compartment. Surgery can result in greater impairment of quality of life than the original prolapse itself (such as the development of new-onset urinary incontinence, or prolapse at a different site). Anterior and posterior prolapse surgery is most common (90 % of operations), but around 43 % of women also have a uterine (34 %) or vault (9 %) procedure at the same time. There is not enough evidence from randomised controlled trials (RCTs) to guide management of vault or uterine prolapse. The Vault or Uterine prolapse surgery Evaluation (VUE) study aims to assess the surgical management of upper compartment pelvic organ prolapse (POP) in terms of clinical effectiveness, cost-effectiveness and adverse events.

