### Use of prolapse severity score as primary outcome

Traditionally, the primary outcome of prolapse surgery has been considered to be objective (physical) restoration of normal anatomy, judged usually by the surgeon performing the operation (clinician observation). This does not necessarily correlate with women’s subjective prolapse symptoms, but these have been much more difficult to measure, not least because they can be multiple, and cure of one symptom may be accompanied by the occurrence of new symptoms. However, we strongly feel that the primary endpoint must depend on the woman’s symptoms as these alone dictate whether further treatment is requested and required. Hence, as in PROSPECT the primary clinical outcome will be the subjective difference in severity of prolapse symptoms measured using the POP-SS [6, 7].

Primary outcomesThe primary clinical outcome is women’s prolapse symptoms measured using the Pelvic Organ Prolapse Symptom Scale (POP-SS) [6, 7], at 1 year after randomisationThe primary quality of life outcome is the overall effect of prolapse symptoms on everyday lifeThe primary economic outcome measure of cost-effectiveness is incremental cost per quality-adjusted life year (QALY) (QALYs based on the EuroQol five dimensions questionnaire (EQ-5D) data) [10]

Secondary outcomes

Generalimmediate and late postoperative morbidityother adverse effects or complicationsoperating timeblood lossnumber of nights in hospitalnumber of readmissions to hospitalneed for further surgery for prolapse or for urinary incontinencetime to further surgeryrecommendation to a friend, andsatisfaction with surgery

Prolapse outcomessubjective recurrence of prolapsesubjective continuation/recurrence of prolapse symptomsobjective residual prolapse stage (POP-Q) at original sitethe development of new (de novo) prolapse at another site, andneed for other conservative prolapse treatment (e.g. pelvic floor muscle training (PFMT), mechanical device)

Urinary outcomesurinary incontinence (persistent or de novo, and types of incontinence) using the ICI questionnaires [8]voiding dysfunction, andneed for alternative management for incontinence or voiding dysfunction (e.g. PFMT, mechanical devices, surgery, drugs, intermittent catheterisation)

Bowel outcomesconstipation (persistent or de novo), andfaecal incontinence (persistent or de novo)

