### Expected adverse events

In this study the following AEs are potentially expected:

Possible (expected) AEs during or associated with surgery are:injury to organs, blood vessels or nervesexcess blood lossblood transfusion; anaesthetic complicationsdeath

Possible (expected) AEs following surgery are:excess blood losshaematomablood transfusionbowel obstructionconstipationfaecal incontinencethrombosis/deep venous thrombosis/pulmonary embolismurinary tract infection; wound infectionother infection (sepsis, septicaemia, abscess)vaginal adhesionspain (acute or chronic, e.g. pelvic pain/buttock pain/sciatica)new or persistent sexual problems including pain (dyspareunia) and inability to have intercourse (apareunia)perineal scarring/tightness requiring surgery (e.g. Fenton’s procedure)urinary retention/voiding difficulties (requiring conservative intervention, e.g. indwelling or intermittent catheterisation, drugs)urinary retention/voiding difficulties requiring surgical intervention (e.g. loosening/division of tape)new or persistent lower urinary tract symptoms (e.g. urinary incontinence, overactive bladder)granulation tissue (including related discharge or bleeding)skin tag or skin bridgemesh exposure/extrusion which requires no treatment or conservative treatment in clinic only (e.g. trimming, local oestrogens, silver nitrate, antibiotics)mesh exposure/extrusion requiring hospitalisation for surgical removal of part or all of the meshother mesh complications (e.g. clumping); suture removal/trimmingdeath

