### Reporting responsibilities of the CI

When the SAE form is uploaded onto the trial website, the CI or trial manager will be automatically notified. The CI (or trial manager) will report any serious and related and expected (i.e. listed above) SAEs to the sponsor within 14 days of receiving the SAE notification.

If, in the opinion of the local PI and the CI, the event is confirmed as being serious and related and unexpected (i.e. not listed above), the CI or trial manager will notify the sponsor within 24 hours of receiving the SAE notification. The sponsor will provide an assessment of the SAE. The CI (or trial manager) will report any serious and related and unexpected SAEs to the main REC and the DMC within 15 days of the CI becoming aware of it.

All related SAEs will be summarised and reported to the Ethics Committee, the funder and the TSC in their regular progress reports.

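### Whether a reoperation for prolapse counts as a serious adverse event depends on which compartment failed and on local judgement of relatedness

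*Protocol article*

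**What the plan says.** All of the following is in the protocol article.

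- **Safety - definitions** starts broadly: "An adverse event (AE) is defined as any untoward medical occurrence in a participant, not necessarily having a causal relationship". It then removes the disease under study: "Adverse events are not signs or symptoms of the disease being studied (in this case uterine or vault prolapse"). An event is related "if it occurs as a result of a procedure required by the protocol (i.e. prolapse surgery"), and "Unrelated SAEs or AEs will not be recorded". Any overnight or day-case admission makes an event serious. A related, serious event that is not on the expected list needs expedited reporting.
- **Expected adverse events** includes "new or persistent lower urinary tract symptoms (e.g. urinary incontinence, overactive bladder"). It contains no entry for recurrent, residual or new prolapse at any site.
- **Background** (abstract and main text) gives two examples of how surgery can leave a woman worse off: "the development of new-onset urinary incontinence, or prolapse at a different site".
- **Use of prolapse severity score as primary outcome** lists, among the secondary outcomes, residual prolapse stage at the original site, the "development of new (de novo) prolapse at another site", need for further prolapse surgery, and time to further surgery.
- **Reporting responsibilities of the CI** leaves it to the opinion of the local PI and the CI whether an event is serious, related and unexpected. If so, the sponsor is told within 24 hours, and "The CI (or trial manager) will report any serious and related and unexpected SAEs to the main REC and the DMC within 15 days".

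**The concern.** The Background pairs new urinary incontinence with prolapse at another site as known consequences of surgery, but only the first is on the expected list. The disease exclusion covers the apical compartment alone, although anterior and posterior repair is a permitted part of the trial operation and the outcome list treats prolapse failure in any compartment as a matter of effectiveness.

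Two women who each return to theatre because their prolapse surgery failed can therefore be classified differently. One may generate an expedited SAE and the other no adverse event at all. Adverse events are part of the primary objective (Principal objectives), and the DMC may advise on unacceptable safety concerns. The arms are different apical procedures, so the compartment that fails could plausibly differ between them. In that case an SAE comparison would partly reflect where an operation fails and not only how safe it is. Expedited reports of a consequence that the protocol already anticipates could also make genuine safety signals harder to see.

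**Working it through.** The documents state no event rate or count on this point, so there is no figure of the plan's own to reproduce. The check applies the rules in order to two cases.

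| Step | Admission to repair a new or recurrent anterior or posterior prolapse | Admission to repair an apical (uterine or vault) recurrence |
|---|---|---|
| Inside the disease exclusion? | No; only uterine or vault prolapse is named | Yes |
| Adverse event? | Can be | No |
| Serious? | Yes, by admission | Does not arise |
| On the expected list? | No | Does not arise |
| If judged related | Unexpected SAE: sponsor in 24 hours, REC and DMC in 15 days | Not an adverse event |
| If judged unrelated | Not recorded as an adverse event | Not an adverse event |
| Counted as a secondary outcome? | Yes | Yes |

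The left-hand column has two opposite endings, separated only by a judgement of relatedness. The plan is for about 40 centres, and 45 were open (Trial status). The same event can be an expedited SAE at one centre and absent from the adverse-event record at another.

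**How large could the distortion be?** The reoperation rates and compartment splits below are assumptions; the arm sizes (315 and 140) come from the sample-size sections. Suppose both arms have the same reoperation rate, every non-apical reoperation is judged related, and the apical shares in the two arms mirror each other. Then:

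SAEs per arm = women per arm × reoperation rate × non-apical share.

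| Trial, per arm | Assumed reoperation rate | Assumed apical share, arm 1 / arm 2 | SAEs by formula | Rounded | Fisher exact P |
|---|---|---|---|---|---|
| Uterine, 315 | 5% | 80% / 20% | 3.2 v 12.6 | 3 v 13 | 0.020 |
| Uterine, 315 | 5% | 70% / 30% | 4.7 v 11.0 | 5 v 11 | 0.20 |
| Uterine, 315 | 5% | 60% / 40% | 6.3 v 9.5 | 6 v 9 | 0.60 |
| Uterine, 315 | 3% | 80% / 20% | 1.9 v 7.6 | 2 v 8 | 0.11 |
| Vault, 140 | 5% | 80% / 20% | 1.4 v 5.6 | 1 v 6 | 0.12 |
| Either | any | equal | equal | equal | no distortion |

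Only the first row gives a nominally significant SAE difference from identical reoperation rates, and it needs an extreme split.

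**Reporting load.** If 1% to 5% of the 910 women had surgery for a new prolapse at another site, that would be 910 × 0.01 = 9 to 910 × 0.05 = 46 admissions. This is an upper figure for expedited reports at those assumed rates, because it takes every one to be judged related.

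**The case against.** The strongest reply has four parts.

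1. **Relatedness is not automatic.** A reader might infer that every anterior or posterior reoperation counts as an unexpected serious harm. The documents do not support that. The event must be judged a result of the prolapse surgery, and a later anterior or posterior prolapse may be residual, recurrent or simply progression. This stands. It does not remove the problem, because it replaces a fixed rule with one that can vary by centre.
2. **Apical failures are not lost.** A reader might infer that apical reoperation counts as no harm in the trial. That is true only of the adverse-event tally. Further prolapse surgery, time to it and POP-Q stage at the original site are secondary outcomes in every arm, and the DMC may request any analysis it wants. This stands in full.
3. **A compartment-neutral reading is possible.** An investigator could treat any prolapse as the disease under study. But the protocol spells the disease out in parentheses as uterine or vault, so this reading works against the text, and having both readings available is itself a source of inconsistency.
4. **No pooled SAE total is specified as an endpoint.** Tabulation may properly be left to the SAP and its dummy tables, which are not shown. This stands, so double counting of effectiveness failures cannot be asserted as a fact. The classification and the expected list are fixed in this document, however, and a later table cannot recover an event that a centre judged unrelated and did not record as an adverse event.

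**Conclusion.** The concern holds as a defect of classification. The exclusion and the expected list do not fit the Background or the outcome list. As written, the adverse-event status of a prolapse reoperation depends on the compartment and on local opinion, and SAE counts can mix effectiveness failure with harm.

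The effectiveness comparison is intact, and nothing here touches the primary outcome or its power. The size and direction of any between-arm distortion cannot be derived from the documents. It is nil if failures fall in the same compartments and are judged alike in both arms. The illustration's P of 0.020 rests on an assumed 5% reoperation rate with an 80/20 split and should not be read as an expected effect. The point is worth correcting because adverse events belong to the primary objective and the correction is cheap.

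**What to change.** Reconcile the Background, the secondary outcomes, the safety definitions and the expected list with one rule for all compartments. Either option would do.

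- **Outcome only.** Word the exclusion as pelvic organ prolapse in any compartment, recurrent or new, together with admission to treat it. State that these events are counted only under the prolapse and further-surgery outcomes and are supplied to the DMC by arm. Complications of the repeat operation stay reportable.
- **Expected event.** Add recurrent or new prolapse at any site to the expected list, drop the apical-only exclusion so that all compartments are handled alike, and tabulate these events separately from complications.

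The cost is a sentence or so in the safety sections and matching SAE guidance to sites. No extra data are collected. The small downside of the first option is that prolapse reoperations no longer appear in the SAE totals, though they remain fully reported as outcomes. The change concerns classification and reporting only and does not affect how women are treated.
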